#### Cognitive behavioural therapy for GAD

CBT models of GAD view pathological worry as central to understanding and treating GAD. These models assume that the worry process is a counterproductive avoidance mechanism through which the person tries to avoid unbearable experiences, including certain thoughts and feelings (cf. [29]). Paradoxically, worry can then directly contribute to the amount of anxiety the person actually experiences [11] and lead to unhelpful coping strategies and beliefs about the importance of controlling thoughts and worries. In Dugas and Robichaud’s CBT for GAD model [38], the main experience to be avoided is uncertainty. Worry serves as a means by which to think through possible (negative) outcomes, and possible solutions. However, given the infinite possible set of outcomes and solutions, worry does not resolve, and the increase in anxiety it produces leads instead to further thwarted attempts to problem-solve possible future scenarios.

The cognitive behavioural arm of the study will follow standard CBT procedures used in the treatment of GAD, whilst incorporating the Dugas and Robichaud model [38]. Therapy will be based on an individual case conceptualization of each participant and will involve flexibly employed standard CBT techniques such as self-monitoring, psychoeducation, cognitive restructuring, problem solving, imaginal exposure, and behavioural experiments. The therapy will aim to help clients understand the role of the mutually reinforcing relationship between intolerance of uncertainty and worry in GAD, and it will teach them to be more aware of this in their daily lives. Exposure will focus on imaginal exposure to feared outcomes and imaginal and direct exposure to uncertainty. Participants will also be encouraged to re-evaluate their beliefs around worry and to develop more active problem-solving skills. Participants will be encouraged to consider the developmental sources of GAD in order to contextualise their beliefs about worry as well as their core beliefs about themselves and the world. As with the EFT condition, therapy will last 16–20 sessions; therapists will be instructed to finish therapy at session 16 but will be allowed discretion to clinically judge whether the therapy should be prolonged to a maximum of 20 sessions.

### Therapist training and supervision

It is envisaged that all therapists will have a prior basic training in both approaches as part of their doctoral training in counselling psychology. To further boost their skills in the respective approaches, therapists will be provided with 5 days of training focused on EFT for GAD (facilitated by [name], an EFT trainer accredited by the International Society for Emotion Focused Therapy) and 5 days of training in CBT for GAD (facilitated by [name], course director of the master of science programme in cognitive therapy at Trinity College Dublin [TCD]). In addition, therapists will attend weekly supervision (1 week in EFT, the other in CBT) for a minimum of 8 months before being assessed as adherent to both approaches and thus released to see participants in the trial. Supervision will be provided by [name] for the EFT condition and by [name] and [name] (an assistant professor in clinical psychology with a special interest in CBT) for the CBT condition. Therapists must be deemed competent in the delivery of both interventions (i.e., EFT for GAD and CBT for GAD) prior to seeing participants in the trial. The decision regarding competence will be made by the supervisor(s) in the respective condition. It is intended that supervision will continue during the trial. Ten therapists have been trained, two of which have already left the study.

### Treatment fidelity assessment

In addition to on-going supervision, which will ensure therapist adherence to the respective treatment protocols, we will also conduct an independent assessment of the adherence and competence (fidelity) of the delivered treatments. All sessions will be audio-recorded. The Person-Centred and Experiential Psychotherapy Scale (EFT version) [39, 40] will be used for the EFT condition and the Cognitive Therapy Scale–Revised [41], as applied for GAD, will be used for the CBT condition. One session will be randomly selected for each case (the first two and the last two sessions from each case will not be included in the pool of potential sessions) and rated by an expert in the respective approach. Selected sessions will be rated on both scales to evaluate not just adherence but also appropriate levels of discrimination between the two approaches. To establish reliability, a portion of the sessions will be rated by at least two independent expert raters.

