### Therapists

Therapists will be trained in both EFT for GAD and CBT for GAD. All therapists will randomly deliver both conditions (*see below*), thus random allocation will be nested within therapists. Therapists will be HSE CIPC employees already working routinely within the CIPC service. Optimally all therapists will be counselling psychologists; it is planned that all therapists will have prior training in both CBT and EFT (*see below*). It is envisaged that the interventions will be delivered by at least six therapists. However, given the likelihood that therapists in CIPC may change jobs over the life of the trial (especially in the context of wider changes in recruitment practice within the HSE), we intend to train more therapists than needed to account for possible attrition.

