### Assessor training

Assessments will be conducted by a doctoral-level counselling psychologist and by psychology graduates (typically at master’s level or studying at master’s level) under the supervision of the doctoral-level psychologist. SCID-5-RV, SCID-5-PD and GADSS assessments will be audio-recorded and archived for subsequent evaluation of adherence to appropriate testing conditions. Assessors conducting post-therapy assessments will be blind to the condition the client was in.

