### Sample size

A sample size of 60 participants was determined (using G*Power) [45] on the basis of the comparison between the two active treatments and pre-post within-group comparison. We used a minimum meaningful comparison (moderate effect size; *f* = 0.25) that is used in assessing difference between two treatments (cf. Shapiro [46]), with statistical power of 0.80 and alpha level of 0.05.

We expect that the study is likely to detect change over time within the two active treatments (the pre-post change should be large). It is envisaged, however, that the sample size may be too small to find any difference between the active treatments (often the differences between active treatments are rather small). Because the present project is a feasibility study, exploratory use of the initial comparison data should help in planning a definite non-inferiority trial that could be developed as phase 2 of the present study, with further participants recruited to the two active interventions on the basis of an estimate of the numbers needed to determine definite evaluation.

Practically speaking, there should be a sufficient number of referrals. Annual referral numbers for CIPC Dublin North-East, where the study is hosted, is estimated at approximately 2000 clients, with at least 25% of individuals referred for anxiety problems. Because we will be recruiting over a 2-year period, we anticipate no issue with recruiting 60+ participants from a prospective pool of 1000 clients.

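### As most naturally read, the fidelity plan nests raters within arm, so own-scale rater bias cannot be separated from true discrimination between EFT and CBT; assigning raters by scale would remove this.

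*Protocol article*

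**What the plan says.** The section Treatment fidelity assessment names one scale for each therapy: the Person-Centred and Experiential Psychotherapy Scale (EFT version) and the Cognitive Therapy Scale–Revised. It then states:

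- Sampling: "One session will be randomly selected for each case", with the opening and closing two sessions left out of the draw.
- Rater and scales: the session is "rated by an expert in the respective approach. Selected sessions will be rated on both scales".
- Purpose of using both scales: "to evaluate not just adherence but also appropriate levels of discrimination between the two approaches".
- Double rating: "To establish reliability, a portion of the sessions will be rated by at least two independent expert raters". The second rater's approach is not stated.

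Under Therapists: "All therapists will randomly deliver both conditions". Under Sample size: "A sample size of 60 participants was determined". Under Assessor training, masking is stated for outcome assessment: "Assessors conducting post-therapy assessments will be blind to the condition the client was in". The article gives no figure for rater agreement, rater bias or expected discrimination.

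**The concern.** The sentence on who rates is tied to the approach of the case. The next sentence, in the passive, puts the same sessions on both scales. Read together, an EFT expert scores every EFT session on both scales and a CBT expert does the same for every CBT session. Therapist training and supervision uses *respective* in the same way: competence is decided by the supervisors of each condition. Any difference between arms on a scale would then also be a difference between two groups of raters, who know the arm from the assignment itself.

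This matters more here than in a trial with separate therapists per arm. The same people deliver both therapies and are trained and supervised in both, so blending of the two is a leading threat to the comparison. Adherence is also one of the stated feasibility aims. The two-scale rating is the only independent check on blending that the article describes. If it can look satisfactory because of who did the rating, it gives less reassurance when a finding of comparable outcomes is used to plan the non-inferiority trial.

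**Working it through.** The article states no fidelity figure, so there is nothing to reproduce. Two things can be checked: what the rating design can estimate, and how large a false signal could be under stated assumptions.

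**Inputs from the article.** 60 cases with one session each, hence at most 60 sessions and 60 × 2 = 120 ratings before any double rating. About 30 sessions per arm is assumed.

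**Step 1: estimability.** Take a model with intercept, arm, scale, arm × scale (discrimination), rater approach and rater approach × scale: six terms.

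| Who rates | Rank | Arm and arm × scale estimable? |
|---|---|---|
| A. Own-approach expert, both scales | 4 of 6 | No: rater approach equals arm, and rater × scale equals arm × scale |
| B. Each scale's own expert, both arms | 4 of 6 | Yes: rater approach is aliased with scale, not with arm |
| C. Both experts, both scales, both arms | 6 of 6 | Yes |

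Under A, no analysis of the singly rated sessions can separate discrimination from rater approach.

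**Step 2: which biases survive under A.** Define the contrast D = ½ × [(EFT scale − CBT scale) in EFT sessions − (EFT scale − CBT scale) in CBT sessions], with the scales on a common metric and true discrimination zero.

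- *General leniency L of EFT raters on both scales.* It adds L − L = 0 to the EFT bracket, so D = 0.
- *Own-scale bias b.* The EFT bracket gains +b and the CBT bracket −b, so D = ½ × [b − (−b)] = b.

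**Step 3: size of the own-scale effect (assumed values).** Take a session SD of 0.7 and residual SD of 0.7, so the total rating SD is √(0.49 + 0.49) ≈ 1. The within-session difference has variance 2 × 0.49 = 0.98. The standard error of D is ½ × √(2 × 0.98/30) ≈ 0.128. For b = 0.25, b/SE ≈ 1.96; for b = 0.5, b/SE ≈ 3.91. Simulation with 2,000 runs per setting gave:

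| Own-scale bias b | Leniency L | Mean D under A | Significant under A | Under B | Under C |
|---|---|---|---|---|---|
| 0 | 0 | 0.00 | 5.0% | 4.4% | 5.0% |
| 0 | 0.5 | 0.00 | 4.7% | 5.0% | 5.4% |
| 0.25 | 0 | 0.25 | 49.7% | 5.4% | 5.3% |
| 0.5 | 0 | 0.49 | 96.8% | 4.7% | 4.2% |
| 0.5 | 0.5 | 0.50 | 97.1% | 4.4% | 3.8% |

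**Step 4: a single scale compared between arms.** Here general leniency does not cancel. Assume one expert per arm with leniency SD s, in session-SD units. The arm difference has variance 2/30 + 2s² and is tested against 1.96 × √(2/30). The false-signal rate is P(|Z| > 1.96 × √[(2/30)/(2/30 + 2s²)]):

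- s = 0.2: cut-off 1.32, 18.6%
- s = 0.3: cut-off 1.02, 30.8%
- s = 0.5: cut-off 0.67, 50.1%

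These rates are two-sided. About half of each (9%, 15%, 25%) falls in the direction that would look like good discrimination on that scale.

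**The case against.** **The text does not say who gives the off-approach rating.** This stands. The sentence about both scales names no rater, and the section has just paired one scale with each approach. It can therefore be read as each scale's expert scoring that scale in every session, which is design B, and then the contrast between arms is sound. Operational detail of this kind may also sit in the full protocol. What remains is that the more natural reading gives design A, and the validity of the check depends on which is meant.

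**Leniency is the wrong bias to worry about.** This largely stands. A generally lenient EFT rater lifts EFT sessions on both scales, so the CBT scale would move in the wrong direction and the within-session contrast would be unaffected. The rates in step 4 therefore do not describe the two-scale check. Own-scale bias does survive, but its size is assumed.

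**Fidelity rests on more than this check.** This stands in part. There are five days of training per approach, at least eight months of weekly supervision and competence sign-off before the trial, and supervision is meant to continue. None of these is an independent measure of whether delivered sessions differed.

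**A reader might infer that the check cannot show the therapies were kept apart, or that a comparable result could not be told from contamination.** The documents do not support this. Leniency cancels, own-scale bias is possible but unquantified, and a discrimination effect much larger than any plausible bias would still be informative. The article itself treats the outcome comparison as exploratory and probably too small to find a difference between treatments.

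**Masking is hard.** This stands. An expert will often recognise the therapy from its content, so a bias that depends on the recognised arm could persist under design B. The 4–5% rates for B assume that it does not.

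**Conclusion.** The point holds as a weakness in a stated rating rule, conditional on the natural reading. If the own-approach expert scores both scales, rater approach is fully aliased with arm, and own-scale bias enters the discrimination contrast one for one. With 30 sessions per arm and no true discrimination, an assumed bias of 0.25 or 0.5 rating SD produces a false signal in about 50% or 97% of simulated trials. These are illustrations, because the documents give no bias figure. The rates of about 19%, 31% and 50% apply only to two-sided comparisons of one scale between arms, with one expert per arm and assumed leniency.

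The double-rated portion would break the aliasing only if the second rater came from the other approach. The article does not say so, and gives reliability as its purpose.

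The effect is confined to the interpretation of fidelity. Sample size, alpha and the GAD-7 analysis are untouched. The missing statement on masking of fidelity raters is not counted as an error in a condensed article.

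**What to change.** State in Treatment fidelity assessment that raters are assigned by scale: an EFT expert scores the EFT scale, and a CBT expert the CBT scale, on every selected session from both arms. Use coded recordings without the arm label, and acknowledge that masking will be partial. If a scale has more than one expert, each should receive sessions from both arms.

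Base the discrimination result on the between-arm contrast within each scale. Keep the double-rated portion for reliability, with the second rater using the same scale. Pairing an EFT and a CBT expert there would mix rater error with differences between approaches and weaken that purpose.

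Cost: about 60 × 2 = 120 ratings, as now, and no extra raters. Each expert group listens to about 60 sessions instead of about 30. All sessions are recorded, so the change can be made at any time before rating begins. If this assignment is already intended, one clarifying sentence is enough.

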### Randomisation

Because the organisational structure of CIPC means that it would not always be possible to randomise between therapists (e.g., often only one therapist works in a particular location), the decision was made to randomise within therapists. [name], a member of the research team with no allegiance to either intervention and no involvement in the delivery of either training or supervision, will generate the allocation sequence using an online randomiser. A random sequence (of numbers 1 and 2, corresponding to EFT or CBT) will be generated for each therapist, who will be identified by code and not by name. After SCID-5 assessment (*see below*), and after allocation to a therapist (*see* the next section on patient consent process and assessment), a member of the research team (the trial manager) will contact [name] and request the assignment (either EFT or CBT) for the next participant for the therapist in question.

### Patient consent process and assessment

Participants are recruited from among clients referred to the CIPC service. Referrals are screened centrally for suitability for the service and then allocated to CIPC therapists working in the CIPC area closest to where the client lives. The client then meets a therapist located in that area for an initial assessment. (For the flow of participants, *see* the Consolidated Standards of Reporting Trials diagram in Fig. 1). When a client presents with anxiety difficulties (as assessed by referral report and/or self-report), has a score ≥ 11 on the GAD-7, and in the assessing therapist’s clinical judgement potentially meets criteria for GAD as a principal diagnosis, the therapist will give the client information about the trial. When the client expresses an interest in participation, meets trial inclusion criteria (e.g., stabilised medication regime), and does not meet trial exclusion criteria (e.g., no current risk of suicide or risk of harm to others as measured by the CORE-OM [*see above*]), the therapist will seek client consent to refer him or her to the research team for further assessment. The therapist will provide the client with a copy of both the study information sheet and the consent form and will pass the client’s contact information to the research team. (*Note*: Administration of the CORE-OM is a routine part of the CIPC initial assessment.)

**Fig. 1 Fig1:**
[figure not shown]
Study flow diagram of referral, screening and allocation of participants to the EFT vs CBT for GAD trial. *CBT* Cognitive behavioural therapy, *CIPC* Counselling in Primary Care, *CSS* Client Satisfaction Survey, *CORE-OM* Clinical Outcomes in Routine Evaluation – Outcome Measure, *EFT* Emotion-focused therapy, GAD Generalised anxiety disorder, *GAD-7* Generalised Anxiety Disorder-7, *GADSS* Generalised Anxiety Disorder Severity Scale, *PHQ-9* Patient Health Questionnaire-9, *SCID-5-PD* Structured Clinical Interview for DSM-5 Personality Disorders, *SCID-5-RV* Structured Clinical Interview for DSM-5 Disorders (Research Version)

After a cooling-off period (1–2 days) the research team will contact the client to schedule an assessment appointment. At the beginning of this appointment, the research team member will discuss the study with the client, address any queries arising from their perusal of the information sheet, and seek consent to proceed with the assessment process. Assessment will involve administration of the SCID-5-RV and the Structured Clinical Interview for DSM-5 Personality Disorders (SCID-5-PD) [42]. In addition, the research team will administer the Generalised Anxiety Disorder Severity Scale (GADSS) [43] and the Patient Health Questionnaire-9 (PHQ-9) [44]. When assessment indicates GAD as a principal diagnosis, and when inclusion criteria are confirmed as being met, the client will be invited to participate in the study. Time will then be taken to address any queries the client may have, and the client will be asked to sign the study consent form.

Those individuals who proceed to become study participants will be allocated a unique trial code. They will be referred to their trial therapist and, only after allocation to a therapist, will be assigned to either the EFT or CBT condition. (Whilst typically the trial therapist will also be the therapist who initially screened the participant, in some exceptional circumstances the trial therapist may not have conducted the initial screening.)

It is anticipated that the first therapy session will typically take place 1 week after the assessment appointment with the research team. Post-treatment assessments will take place at week 16 (i.e., as close as possible to 16 calendar weeks from the date of the first session) and 6 months after 16 weeks (as close as possible to 42 calendar weeks from the date of the first session). In addition, when participants finish therapy outside the range of 16 ± 2 weeks (i.e., ≤ 13 weeks or ≥ 19 weeks), an additional assessment will be carried out post-therapy (i.e., as close as possible to the date of the last session). Sixteen-week, post-therapy and 6-month follow-up assessments will consist of administering the GAD-7, GADSS, CORE-OM and PHQ-9. In addition, the Counselling in Primary Care Client Satisfaction Survey (CIPC-CSS), which is routinely administered to all CIPC clients at the end of therapy, will be administered (*see below* for a description of measures).

If, during the course of the treatment, any client’s clinical condition suggests another course of treatment (e.g., further assessment, hospitalisation, acute risk management), this will be provided as per typical CIPC service guidelines. [name] (CIPC Director of Counselling) and the counselling co-ordinators who conduct regular clinical supervision will oversee any clinical issues arising. It has been agreed with CIPC that if, during follow-up assessment, any participant presents at risk or in significant distress, the research team will contact both CIPC and the participant’s GP to inform them of same.

### Measures

#### Screening and assessment of participants

Potential participants will be screened for generalised anxiety using the GAD-7 (*see below*), with a score ≥ 11 indicating that an individual may be eligible for the study. Potential participants will then be assessed with the SCID-5-RV and the SCID-5-PD. The SCID-5-RV is a semi-structured diagnostic interview for assessing the major *Diagnostic and Statistical Manual of Mental Disorders, Fifth Edition* (DSM-5) diagnoses, while the SCID-5-PD is a semi-structured diagnostic interview for assessing the ten DSM-5 personality disorders. During assessment, demographic data (including age, gender, relationship status, living arrangements, number of dependents, level of education attained, occupation and work history, disability) as well as data related to presenting issues (including history of present and other psychological difficulties, current and past interventions, medication, substance use) will be gathered. A summary of assessments is presented in Fig. 2.

**Fig. 2 Fig2:**
[figure not shown]
Standard Protocol Items: Recommendations for Interventional Trials (SPIRIT) diagram of enrolment, intervention and assessment. *CIPC CSS* Counselling in Primary Care Client Satisfaction Survey, *CORE-OM* Clinical Outcomes in Routine Evaluation – Outcome Measure, *GAD-7* Generalised Anxiety Disorder-7, *GADSS* Generalised Anxiety Disorder Severity Scale, *GP* General practitioner, *PHQ-9* Patient Health Questionnaire-9, *SCID-5-PD* Structured Clinical Interview for DSM-5 Personality Disorders, *SCID-5-RV* Structured Clinical Interview for DSM-5 Disorders (Research Version)

